## Abstract

**Background:**

The rate of individuals with addiction who are currently treated are low, and this can be explained by barriers such as stigma, desire to cope alone, and difficulty to access treatment. These barriers could be overcome by mobile technologies. EMI (Ecological Momentary Intervention) is a treatment procedure characterized by the delivery of interventions (messages on smartphones) to people in their daily lives. EMI presents opportunities for treatments to be available to people during times and in situations when they are most needed. Craving is a strong predictor of relapse and a key target for addiction treatment. Studies using Ecological Momentary Assessment (EMA) method have revealed that, in daily life, person-specific cues could precipitate craving, that in turn, is associated with a higher probability to report substance use and relapse in the following hours. Assessment and management of these specific situations in daily life could help to decrease addictive use and avoid relapse. The Craving-Manager smartphone app has been designed to diagnose addictive disorders, and assess and manage craving as well as individual predictors of use/relapse. It delivers specific and individualized interventions (counseling messages) composed of evidence-based addiction treatments approaches (cognitive behavioral therapy and mindfulness). The Craving-Manager app can be used for any addiction (substance or behavior). The objective of this protocol is to evaluate the efficacy of the Craving-Manager app in decreasing use (of primary substance(s)/addictive behavior(s)) over 4 weeks, among individuals on a waiting list for outpatient addiction treatment.

**Methods/design:**

This multicenter double-blind randomized controlled trial (RCT) will compare two parallel groups: experimental group (full interventional version of the app, 4 weeks, EMA + EMI), versus control group (restricted version of the app, 4 weeks, only EMA). Two hundred and seventy-four participants will be recruited in 6 addiction treatment centers in France.

**Discussion:**

This RCT will provide indication on how the Craving-Manager app will reduce addictive use (e.g., better craving management, better stimulus control) in both substance and behavioral addictions. If its efficacy is confirmed, the app could offer the possibility of an easy to use and personalized intervention accessible to the greatest number of individuals with addiction.

**Clinical Trial Registration:**

ClinicalTrials.gov: NCT04732676.

## Introduction

1.

Substance use disorders and addictive non-substance disorders (that we combine under the term addiction) are the most prevalent psychiatric disorders in the general population (1–4) and are associated with significant medical and social harm (5). Addiction is defined as a loss of or reduced control of use of a reinforcer (substances or behaviors) that translates into continued use despite its harmful consequences (6, 7). Addiction may be considered a chronic disease (8, 9), and relapse is the major clinical outcome and the focus of treatments (10). Contemporary definitions of addiction emphasize on the inability to limit use despite the clearly negative consequences, as well as the overwhelming desire to use, also named “craving” or “pathological craving” (7). Craving is an unwanted, persistent, and intense desire to use the substance, or engage in a behavior. It is currently considered a central component in several addiction models (11, 12) and was introduced as a diagnostic criterion in the Diagnostic and Statistical Manual of Mental Disorders, Fifth Edition–DSM-5 (6, 7, 13, 14). Craving can be considered as a complex subjective phenomenon strongly influenced by internal factors and environmental context and its expression fluctuates, in duration and intensity, within hours (15, 16).

The major role of craving in relapse has been highlighted by numerous studies for both substance and non-substance addictions (17, 18). Based on such research, craving is currently considered a major treatment target (7, 19). Some factors may contribute to induce craving, and therefore increase the risk for relapse. In particular, studies have experimentally demonstrated the ability of certain stimuli (cues) previously associated with substance use (such as syringes, bottle, smoke, etc.) to induce physiological responses and to increase craving in the absence of the substance (20–23) as well as the activation of brain reward system (24, 25). Similar responses have also been demonstrated for gambling (26, 27) and food addiction (28). These responses, also referred to as “cue reactivity,” are remarkably stable and are specifically induced by stimuli associated with substance use but not by neutral stimuli (20). This reactivity seems to persist long after cessation of use (29, 30). Although the relationship between these phenomena and relapse has long been controversial, laboratory data showed a link between the intensity of the craving episode induced after exposure to these stimuli, and relapse for tobacco, alcohol, cocaine and heroin use (22, 31–35).

In addition to these so-called “standard” cues, linked to the substance itself or related paraphernalia (i.e., equipment necessary for substance use), there are also more complex and varied stimuli, specific to each subject’s personal history and substance use habits. These “person-specific” cues correspond to a variety of experiences, contexts, environments or emotions, associated with addictive use and specific to each subject. Exposure to these person-specific cues is associated with higher levels of craving than exposure to standard stimuli, both in laboratory (36), and in individuals’ natural environment (37). Ecological Momentary Assessment (EMA), a method that uses mobile technologies for collecting real-time data in daily life (38), has confirmed the predictive nature of exposure to these conditioned stimuli on craving intensity and later substance use over the following hours, regardless of the type of substance or behavior considered (21, 37, 39, 40). In addition, analyses showed that most subjects remained exposed to these person-specific stimuli during the first weeks of treatment, in a more pronounced way than stimuli directly related to substances that could be easier to avoid (37, 39).

Treatment of substance use disorders/behavioral addictions aims to reach and maintain abstinence, or at least a significant reduction in addictive use, by avoiding or controlling high-risk situations for relapse. As a major predictive factor for relapse, craving management can be an important target for pharmacological and psychosocial treatments developed in this field (41). Psychotherapies, in particular, cognitive-behavioral therapies (CBT), as part of a comprehensive approach to addiction treatment, are pragmatic interventions allowing evaluation and awareness of the mechanisms involved in recovery and relapse (42). CBTs aim to help the subject to analyze the usual contexts and emotions related to addictive use (exposure to stimuli, proposal of use by a peer, conflict situation, etc.) and to identify high-risk situations for relapse. CBTs then provide cognitive and behavioral strategies to cope with these situations, for example by highlighting negative consequences of use, and positive aspects of abstinence. These treatment approaches have demonstrated the ability to induce changes at the neurobiological level (43) and improve clinical outcomes (44, 45). Among the mechanisms underlying the impact of these interventions, coping strategies and the subject’s ability to anticipate and manage these at-risk situations have been identified as determinant factors (45–47).

Despite high prevalence in the general population, and the effectiveness of treatments, addiction is the psychiatric disorder with the most important “treatment gap,” i.e., the difference between the prevalence of a disorder and the number of individuals treated for that disorder (48). Indeed, the worldwide proportion of individuals with an addiction accessing treatment is estimated to be less than 25% overall, and less than 10% for alcohol and tobacco (49–52). This gap could be partially explained by a lack of insight, i.e., capability to recognize one’s mental illness, its symptoms and consequences, and to perceive the need for treatment (53, 54). Stigma associated with addiction, the desire to try to cope alone, but also the lack of knowledge about the treatment of addictive disorders could also impede access to treatment (55). This gap could also be explained by structural barriers, such as difficulties for some people to access standard treatment centers, e.g., rural areas, or time demands. However, delayed access to treatment could lead to an increase in addiction severity, associated with more complications, and poorer treatment outcomes (56).

Some of these barriers can be overcome by the use of mobile technologies. Mobile health (mHealth) offers new opportunities to improve prevention, screening, diagnosis and treatment of addictions (57). A number of people could benefit from screening and diagnostic tools easily accessible and anonymous, and smartphone apps could be designed for individual autonomous use, and reach large portions of the population who would otherwise not have access to a standard treatment. Ecological Momentary Intervention (EMI) is a treatment procedure characterized by the delivery of interventions, generally by messages on smartphones, in response to EMA self-reports in the app, to people as they go about their daily lives (ecological) and in the moment when it is most needed (momentary) (58, 59). For example, in addiction treatments, EMI apps may help to protect against relapse by prompting people to mobilize their coping resources in high-risk situations. Populations underserved or reluctant to face-to-face traditional treatment could benefit from such accessible technology (60, 61). For example, it has been demonstrated that a larger proportion of female, younger or older adults, or at-risk users access internet-based interventions than are typically seen in traditional treatment contexts (62–65). Thus, EMI presents cost efficient opportunities for treatments to be available to more people during times and in situations when they are most needed, without the need to consult a specialist (66).

A growing number of mobile medical interventions apps are being developed in all health areas (59, 67), including mental health (58, 68, 69). Several reviews have investigated apps targeting addictions [e.g., (70–72)], and some of them reported encouraging results for tobacco (72) and alcohol (73–76). Although fewer in number, apps targeting illegal substances also show promising results in reducing craving or use of cannabis (77–79), opioids (80), or various substances (81). However, the reduced number of available studies of high methodological quality or with sufficient statistical power (82), as well as heterogeneity in comparison conditions, outcomes or population tested, make it difficult to provide compelling evidence of efficacy upon abstinence or reduction of addictive use (69, 71), despite good feasibility and acceptability (68). This greatly limits for now their dissemination and adoption in the medical community (66, 83).

Nevertheless, these studies give us some indication for best outcomes. Among the major pitfalls frequently reported in mHealth apps (84, 85), difficulty to maintain engagement is important, and could be explained by design considerations, and user experience. For example, too frequent or too long EMA assessments can lead to user fatigue and discontinuation of use. On the contrary, simplicity, and easily accessible information have been identified to enhance user engagement (81, 86). Regular utilization is important because it contributes to the effectiveness of mHealth app, but, interestingly, could also be sustained by the user’s perception of effectiveness (87, 88). Tailored content and personalization could enhance the feeling of being concerned and consequently promote user engagement. Indeed, “one size fits all” interventions could miss the point, and addiction management has been shown to be more effective when treatments were personalized to target the specific needs and characteristics of each patient (89, 90). As previously mentioned, currently available research suggests that exposure to complex stimuli associated with using a substance/engaging in the addictive behavior, and linked to individuals’ unique history may represent a major predictor of relapse. The use of geolocation, for example, could contribute to detect, for each individual, the places most associated with addictive use (potentially increasing the risk of further relapse), and thus allow to define, in a personalized way, when to propose an intervention (91). In this line, Just-In-Time Adaptive Interventions (JITAIs) propose to adapt, improve and tailor the treatment delivery based on previous answers provided by the user, or information collected by the smartphone (92, 93).

Another crucial aspect for acceptability and dissemination of mHealth apps is their scientific and medical support (94, 95). This can be achieved in several different ways: by involving users and experts in the development of the app, but also by informing about the theoretical framework and/or evidence-based approaches on which the app and its content are based (85). For example, use of the Behavior Change techniques (BCTs) taxonomy (96) could help to describe active “ingredients” of the intervention (97) and could provide further exploration of its mechanisms of action in efficacy studies (98). For management of addictions, some BCTs have been reported as particularly efficient: “Avoidance/reducing of exposure to cues for behavior,” “Pros and cons”: listing and comparing the advantages and disadvantages of quitting, “Self-monitoring of behavior” as well as “Behavioral substitution”: engaging in alternative activities (99, 100).

In this context, we developed the Craving-Manager smartphone app targeting craving and personal situations at-risk for addictive use for people with addiction, whatever the addiction, substances and behaviors. This article describes the protocol for a multicenter randomized double-blind controlled trial with the primary objective of evaluating the efficacy of 4 weeks of use of the Craving-Manager app, as compared to a restricted version of the app (EMA only - placebo), among individuals on a waiting list for outpatient addiction treatment. We hypothesized that, in comparison to those receiving the restricted version of the app, those receiving the Craving-Manager app will be more likely to decrease the use of primary substance/addictive behavior over the 4 weeks use of the app.

## Methods and analysis

2.

### Design

2.1.

This study is a randomized double-blind controlled trial comparing two parallel groups. The intervention consists of 4 weeks of use of the Craving-Manager app. The control group will receive a restricted version of the app (EMA only). The study was registered on ClinicalTrials.gov (NCT04732676), and was approved by French Ethics Committee on 31 March 2021 (ID-RCB 2020-A01707-32).

### Participants

2.2.

Participants will be recruited among people requesting treatment for addiction in one of 6 specialized addiction treatment centers in France (Bordeaux, Bayonne, Limoges, Poitiers, Grenoble, La Réunion). Recruitment will take place before the beginning of standard treatment, while waiting for the first appointment. Eligible participants will be adults with at least one substance or behavioral addiction (including any addictive use/ behavior for which the participant feels a loss of control and/or that may lead to the need to seek addiction treatment*)*, who request help for that addiction, and with more than a 1-month-delay on the waiting-list before the first appointment. Participants should not have difficulty in understanding and writing French, and should be familiar with the use of a smartphone. Written consent will be collected after an informed consent procedure. Exclusion criteria concern people with somatic, cognitive or other disorders preventing the use of smartphone (deafness, impaired vision, illiteracy....), or people with medical, psychiatric or addictive disorders that warrants immediate treatment. People who are deprived of liberty due to an ongoing legal procedure, individuals under legal protection, under guardianship or curatorship, or not affiliate/ beneficiary of a social security scheme will not be included in the study in compliance with French Regulations on the participation of Humans in research.

### Sample size calculation

2.3.

A power analysis was performed to determine the sample size based on data from a previous EMA study among subjects beginning outpatient addiction treatment (101). We considered that a significant clinical effect was a decrease of at least 20% of addictive use frequency for 20% of the participants in the experimental group between the 1st and 4th week of smartphone app use. We expect that 5% of participants in the control group will present this decrease. To observe a difference of 15% (20% vs. 5%), with a 90% statistical power, a type 1 error rate of 5% and assuming 20% loss-to-follow-up (considered as failures), we need 137 participants randomized to each group (274 participants to be included in total).

### Randomization and blinding

2.4.

Participants will be randomized in two distinct groups: the Experimental Group will have access to the full active version of the Craving-Manager app (EMA and EMI) during 1 month, and the Control Group will have access to a restricted (placebo) smartphone app (EMA only) during 1 month.

Randomization will be done by the app, and will take place after confirmation of eligibility and the informed consent procedure. It will be done centrally in a 1:1 ratio, and stratified by inclusion center.

Participants will be unaware of the specific goals of the study or of the differences between the 2 versions of the app. The primary endpoint will be collected through EMA. Research staff will be unaware of group assignment and secondary endpoint collected through face-to-face interviews will be assessed blindly to the randomization group.

### Measurements

2.5.

Data will be collected through different questionnaires: the Addiction Severity Index (ASI), the Mini International Neuropsychiatric Interview (MINI), a Craving Evaluation scale, the Treatment Service Review (TSR), Feasibility and acceptability questionnaires, and some data will be directly collected by the smartphone app (see 2.7 Craving-Manager app).

The Addiction Severity Index (ASI) is a semi-structured interview to assess impairments that commonly occur due to substance-related disorders (102). The modified and validated French version of the ASI (m-ASI) will be used to take into account tobacco and addictive behaviors (103). The m-ASI explores six areas that may be affected by addiction: medical status, employment/support status, substance and behavioral addiction, family and social relationships, legal status, and psychological status.

The Treatment Service Review (TSR 6th version) is an inventory of the subject’s medical, psychosocial and psycho-educational contacts over the past 30 days (104).

The Mini International Neuropsychiatric Interview (MINI) is a structured diagnostic interview providing standardized assessment of major psychiatric disorders defined according to DSM criteria (105). For this study, we have adapted the French DSM-IV version of the MINI to meet DSM-5 criteria (6). Diagnoses of Substance Use Disorders (SUD), gambling disorder and internet gaming disorder will be explored with the DSM-5 criteria (with addition of the craving criterion as an exploratory measure for gambling and gaming). For other addictions (any other use/addictive behavior for which the participant feels a loss of control and/or that may lead to the need to seek addiction treatment), the DSM-5 diagnostic criteria for SUD will be adapted to the use/behavior concerned.

The Craving Evaluation scale, developed by the SANPSY lab at University of Bordeaux, explores craving for all substances and addictive behaviors reported by the participant: the frequency of craving, corresponding to the number of days craving was experienced during the past 30 days, as well as mean and maximum craving intensity on a numerical rating scale ranging from 0 (no craving) to 10 (extreme craving).

The Acceptability E-scale (AES) is a 6-item questionnaire that evaluates the extent to which participants find e-health systems acceptable. Each item is ranked on a 5-point Likert scale, generating a total score of acceptability ranging from 6 (lowest acceptability) to 30 (highest acceptability) (106).

The Digital Working Alliance Inventory (D-WAI) measures factors (goals, tasks and bond) to examine the therapeutic relationship between the participant and the app (107).

The user version of the Mobile Application Rating Scale (uMARS) is a simple tool that can be reliably used by end-users to assess the quality of mHealth apps (108). A translation has been published by the French National Health Agency (Haute Autorité de Santé) (109).

The Client Satisfaction Questionnaire (CSQ-8) is a multi-item measure of satisfaction related to healthcare (110, 111). The CSQ-8 total score ranges from 8 to 32. A higher score represents greater satisfaction.

Toxicological measurements will be systematically associated with the m-ASI, as previous research has found that the validity of self-report information on substance use is increased when biological assessments are included in the research protocol (112): Urinalysis (to detect opioids, methadone (EDDP), cocaine, benzodiazepines, cannabis and buprenorphine), alcohol and CO breath tests.

### Study procedure and intervention

2.6.

Participants will be recruited among patients on a waiting list for a first clinical appointment at the inclusion center, with at least 1-month delay before the first scheduled appointment (to avoid overlap of the intervention proposed by the Craving-Manager app with the intervention that will be provided later by the addiction clinic; Figure 1). First, a telephone screening interview will allow to explain the study and to check the main inclusion criteria. Then, interested and eligible participants will receive an inclusion visit (baseline) at the inclusion center to sign the informed consent, and receive a face-to-face research interview, with ASI, MINI, TSR and Craving Evaluation scale (see Table 1).

**Figure 1 fig1:**
[figure not shown]
Description of study interventions and evaluations by group.

**Table 1 tab1:** Assessment procedure according to each visit.

	Screening	Baseline (M0)	Smartphone app	1-month Follow-up (M1)	4-month Follow-up (M4)
Criteria verification	x	x			
Informed consent		x			
Inclusion		x			
Randomization		x			
ASI		x		x	x
Craving scale		x		x	x
TSR		x		x	x
MINI		x			
Toxicological measurements		x		x	x
EMA			x		
EMI			x (for experimental group only)		
AES				x	
D-WAY				x	
uMARS				x	
CSQ-8				x	

They will then receive a smartphone loaned for the study, containing the app. The randomization will be performed by the app, and will allow to unlock one of the 2 versions of the app: a restricted version (EMA only–placebo) for the Control Group, and a full active version of the Craving-Manager app (EMA and EMI) for the Experimental Group (see below). The use of a restricted version of the app in the Control group is intended to control for potential increase in empowerment or insight as a result of answering self-questionnaires. Indeed, previous studies have documented the positive impact of the self-monitoring on substance use reduction in EMA protocols (113).

All participants will be trained to use the smartphone. As the Craving-Manager app has been designed to be used as a stand-alone app, several tutorials are provided while the app is being used. The completion of the app questionnaires is done in autonomy by the participant, but a research assistant (dedicated to the technical aspects only and not involved in participant assessment, to maintain the blindness) is available to answer any questions and provide help, if needed. Participants from both groups will receive training, and they will not be aware of the differences between the 2 versions of the app.

The app will be active for 4 consecutive weeks and then it will be automatically deactivated. At the one-month follow-up, the smartphone will be returned and all participants will receive a face-to-face research interview evaluation with ASI, Craving Evaluation scale, and feasibility, acceptability and Intervention Satisfaction scales (AES, D-WAI, uMARS, CSQ-8).

At the 4-month follow-up, participants will receive a face-to-face research interview evaluation with ASI, TSR and Craving Evaluation scale. Financial compensation will be provided as a function of visits completed (with a maximum of 120 euros for full participation), but regardless of frequency of app use, to avoid influencing completion rate.

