### Analysis strategy

2.8.

The primary objective to evaluate the efficacy of the Craving-Manager app over 4 weeks, as compared to a restricted (placebo) version of the app, will be assessed by comparing the percentage of participants for whom a 20% decrease in frequency of use of primary substance/ addictive behavior was observed, between the 1st and 4th week of smartphone app use, in the experimental group versus the control group. This 20% reduction threshold was defined in line with decrease in the “percentage of using days” observed with smartphone apps targeting alcohol (75) and substance use disorders (80).

Analyses will be conducted according to the intent to treat principle, in which all randomized participants will be included in the group in which they were first randomized and all their data will be used, regardless of the changes over the study duration.

In addition, in case some participants stopped using the app before the expected termination, a sensitivity analysis will be performed using the LOCF (Last Observation Carried Forward) approach, to calculate the decrease in frequency of use of primary substance/behavior not on the 4^th^ week, but on the last 7 days with at least one EMA questionnaire completed.

The comparison between groups will focus on the proportion of participants that reach a 20% decrease in use of primary substance(s)/ addictive behavior(s). This is a superiority trial (bilateral test). The 95% confidence intervals (exact binomial distribution) in each group will be calculated. These 2 proportions will be compared with a Chi2 test or with Fisher’s exact test, according to the size of the expected values under the hypothesis of independence. Mixed effects logistic regression model will be used to adjust stratification factor (random effect on centers) and other major confounding factors. Assumption of the models (log-linearity of the associations) will be systematically checked.

Efficacy of the intervention will also be examined on secondary endpoints: Multifactorial addiction severity (assessed with ASI Composite Score for the primary addiction) at 1-month and 4-month follow-ups, and craving self-reported in the last EMA week, and reported at 1-month and 4-month follow-ups in the Craving Evaluation Scale.

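### The 1-month interview puts four app-evaluation scales alongside the blinded ASI and craving assessments, which can unblind the assessor at M1 or M4

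*Protocol article*

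**What the plan says.** Section 2.4 (Randomization and blinding) gives a general assurance: "Research staff will be unaware of group assignment and secondary endpoint collected through face-to-face interviews will be assessed blindly to the randomization group". It sets no end date and makes no exception for any visit.

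Section 2.8 (Analysis strategy) names the endpoints that this covers. One is "Multifactorial addiction severity (assessed with ASI Composite Score for the primary addiction) at 1-month and 4-month follow-ups". The Craving Evaluation scale is the other, at the same two visits.

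Section 2.6 (Study procedure and intervention) describes M1, the visit at which the phone is returned, as a "face-to-face research interview evaluation with ASI, Craving Evaluation scale, and feasibility, acceptability and Intervention Satisfaction scales (AES, D-WAI, uMARS, CSQ-8"). Table 1 places all of these at M1 and adds the TSR. The M4 visit is a "face-to-face research interview evaluation with ASI, TSR and Craving Evaluation scale".

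Section 2.5 (Measurements) says what the app scales cover. The D-WAI is used "to examine the therapeutic relationship between the participant and the app", and the uMARS "can be reliably used by end-users to assess the quality of mHealth apps". The AES measures acceptability and the CSQ-8 satisfaction.

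Section 2.6 also separates one staff role. The research assistant who helps with the app is "dedicated to the technical aspects only and not involved in participant assessment, to maintain the blindness".

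**The concern.** The two versions of the app are the only thing that distinguishes the arms, and the M1 interview asks the participant to evaluate that app in the same session as the blinded assessments. A participant who comments on coping messages or location alerts points to the experimental arm. One who says that the app only asked questions points to the control arm.

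The ASI is a semi-structured interview, so an assessor who knows the arm may probe or score differently without meaning to. At stake is the blind assessment of the interview-based secondary efficacy endpoints. The Discussion counts the double-blind design among the trial's strengths.

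**Working it through.** No arithmetic applies: the point depends on no sample size, power or error rate. The check is whether the passages, read together, secure the blinding that section 2.4 asserts.

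1. **Is the assessor meant to be blind for these measures?** Yes. Section 2.4 covers secondary endpoints from face-to-face interviews, and section 2.8 places the ASI composite score and the Craving Evaluation scale among them at M1 and M4. That blinding should last through M4 is an inference from these two sections; no time limit is stated.

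2. **Are the app scales in the same session?** Yes, as written. Section 2.6 lists them inside the same M1 interview as the ASI and craving scale.

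3. **Would talk about the app distinguish the arms?** It could. Under section 2.7, only the experimental arm receives intervention messages, a conversational agent, a map of at-risk places with location-triggered messages, and weekly personalised feedback on cues, craving and use. The control arm answers the EMA questionnaires and receives feedback on completion only.

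4. **Does a stated safeguard close this route?** No. The separated technical assistant covers help with the app. For the four scales, the article gives no order, no mode of completion and no separate collector. Participants are not told how the versions differ, but this protects the participant's blinding more than the assessor's: someone unaware that a feature marks the arm has no reason to keep quiet about it.

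5. **Which ratings are exposed?** This turns on two facts that the article does not give:
   - App scales first, same assessor at M4: M1 and M4 are both exposed.
   - App scales first, different assessor at M4: M1 is exposed; M4 is not, provided nothing is passed on.
   - App scales last, same assessor at M4: M1 is protected from this route; M4 is exposed.
   - App scales last, different assessor at M4: neither is exposed by this route, on the same proviso.

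   Section 2.6 names the ASI and craving scale before the app scales, but a list is not a stated order of administration.

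6. **Which endpoints are sensitive to an unblinded assessor?** Mainly the ASI. The Craving Evaluation scale is a count of days and 0 to 10 ratings given by the participant, so the interviewer has less room to influence it. The primary endpoint is collected through EMA (section 2.4) and does not pass through either interview.

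**The case against.** The strongest reply is that the article does not show blinding to fail. Both arms complete identical scales, and a rating carries no arm label. The AES is described as a questionnaire and the uMARS as a tool for end-users, so both may be self-completed at the visit. Order of forms and who handles them are details that an article commonly leaves to the full protocol, which is not shown. Toxicological tests accompany the ASI and give some objective support for the substance-use information.

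Much of this stands. A reader might infer that the M1 interview reveals the arm, that all M4 interview endpoints are then rated unblinded, and that the bias favours the app. The documents support none of these:

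- Unblinding needs the participant to say something revealing, and no such discussion is described.
- Exposure at M4 needs the same assessor to return, which is not stated.
- The direction of any bias is not shown.
- Phone return and reasons for stopping cannot be counted as part of the assessor's interview. Section 2.6 does not say who receives the phone, and section 2.8 does not say who records the reasons.

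The reply does not dispose of the point, because the article is not merely silent. Section 2.6 places the app scales inside the interview that also yields the blinded endpoints. Followed as written, that arrangement works against the assurance that a "secondary endpoint collected through face-to-face interviews will be assessed blindly to the randomization group". The sponsor already separates app support from assessment for this very reason, and M1 is where the participant is asked directly about the app.

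**Conclusion.** The point holds as a risk to assessor blinding, not as a demonstrated failure. The M1 interview can unblind the assessor: at M1 if the app scales precede the ASI and craving scale, and at M4 if the same person assesses again. It concerns secondary endpoints only, chiefly the ASI composite score. Any participant who attends M1 could be affected (at most the 274 planned), but the number actually unblinded, and the size and direction of any bias, cannot be determined from the document.

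The conclusion assumes that section 2.6 describes the visit as it will be run, and that assessors know the design well enough to recognise arm-specific features. If the full protocol already has the scales self-completed out of the assessor's sight after the rated interviews, and withholds the answers, one clarifying sentence is enough. Otherwise the correction is worth making, because the trial relies on this blinding and protecting it costs very little.

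**What to change.** In section 2.6:

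- Take the AES, D-WAI, uMARS and CSQ-8 out of the assessor's M1 interview.
- Have participants complete them alone, electronically or on paper in a sealed envelope, after the ASI, TSR and Craving Evaluation scale are closed.
- Withhold the answers, and any recorded reasons for stopping, from the assessor until that participant's M4 interview is complete.
- Ask participants at the start of M1 and of M4 not to describe the app to the interviewer.

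The technical assistant need not collect the scales. Section 2.6 limits that role to technical matters, and participants may rate the app more kindly when handing the form to the person who helped them use it.

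The cost is a minor change in visit order and form handling. No extra staff, visits, instruments or participants are needed.
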